#### CTC Implementation Measures

Community board surveys. To monitor the community mobilization process, 20 CTC community board members in the intervention communities will be surveyed annually by phone using a revised Community Board Survey instrument initially developed by SDRG for the Oregon TOGETHER! project and the current CRD Coalition Questionnaire. The first survey will be conducted approximately 8 months after the CTC intervention is initiated. The CTC Board Survey will assess dimensions associated with developing and maintaining an effective community board (Gottlieb et al., 1993; Harachi Manger et al., 1992; Kumpfer et al., 1993; Moos, 1974; Prestby & Wandersman, 1985; Prestby et al., 1990): board membership, meeting schedule, meeting attendance, organizational structure, board cohesiveness, board leadership, task focus, planning products, use of data, perceived board cohesion, board efficacy, board member knowledge and skills, resources generated, leadership support, participation costs and benefits, member satisfaction, member recruitment and orientation, and continued involvement of key community leaders. The CTC Board Survey instrument has been tested with 35 community risk reduction planning boards, and scales have demonstrated good internal reliability (scale alpha coefficients ranging between .62 and .96) (Harachi Manger et al., 1992). (See Appendix B for Community Board survey instrument and CRD Coalition instruments.) This survey instrument will be expanded to incorporate constructs of community board functioning shown to predict higher implementation in recently completed studies evaluating the effectiveness of CTC boards (e.g., Greenberg et al., 1999) and other community prevention coalitions (e.g., Kegler et al., 1998).

Board activity reports and strategic plans. Monthly reports from each community coordinator to the project director will document the community board, task force, and staff activities and will include meeting minutes and attendance records. Copies of strategic plans will document community assessment, plans for implementing tested interventions, and evaluation plans.

Intervention implementation measures. In the intervention communities, monitoring of preventive intervention implementation will be an ongoing process to ensure that the interventions chosen by the community prevention boards achieve the integrity, scope, and intensity necessary to achieve the community's risk reduction and protective factor enhancement objectives. For each intervention, measures of implementation integrity and intensity will be obtained from the original testers of the intervention (see Appendix B for an example implementation checklist). Implementation standards will be specified for each intervention prior to implementation, though the specific implementation measures used in each community will vary depending on the interventions selected by the community board. These measures will be used to assist the intervention communities to monitor their progress in implementing the evidence-based interventions described in their community prevention plans. The feedback provided by these measures will be used to support the continuous quality improvement component of Phase V of the CTC intervention (Wandersman et al., 1998).

Community board training. Pre- and post-test questionnaires will be administered at each community board training session to assess knowledge gain, attitude change, and consumer satisfaction information. These questionnaires will be used to evaluate the quality of the CTC training programs provided by DRP.

Documentation of non-intervention community influences. Characteristics of each community in both the intervention and control conditions that might influence the community mobilization process or community prevalence of adolescent behavior problems will be obtained from the key informant survey described previously. Also, any major changes or events in the community that might affect program implementation (e.g., changes in community policies, layoffs by a major employer) or prevention efforts in the community will be documented using field staff logs and the key informant interviews.

## Data Preparation and Management

Data management activities for all data will involve computerizing records, cleaning and insuring the quality and completeness of the data, providing basic output of frequencies and distributions of data elements, and providing documentation. SDRG's data managers have successfully completed this process for numerous data sets from multiple sites since 1994. Codebooks will include fully annotated questionnaires indicating variable names and values for response codes, an alphabetic variable dictionary that includes variable labels and response codes, program files for creating file architecture, and frequencies and relevant reliabilities for all variables and scales. Auxiliary manuals will include sources of data, cleaning protocols for out-of-range and logical inconsistencies, copies of command files that make permanent file modifications, and full records for created variables and scales with wording and coding of all items used, as well as compute statements for scale construction.

## Analysis

We will apply our experience in creating and maintaining large data sets from multi-site studies to assure that the data obtained in the proposed study are of high quality. We begin our analyses by looking descriptively at the variables to be used and assessing the extent to which the assumptions of the proposed models are violated. Further, measurement models that have already been developed in prior studies will be evaluated in the data set using confirmatory techniques. For those constructs for which the measurement has not been previously validated, psychometric analyses will be conducted to provide strong grounds for conducting the proposed outcome analyses. We recognize the importance of addressing the nested data structure in the measurement as well as analysis of outcomes (James, 1982; Sirotnik, 1980). Psychometric analyses appropriate for the multilevel structure of the data will be used when evaluating the measurement of individual level variables (James, 1982; Kreft, 1993; Muthén, 1989, 1991, 1994; Raudenbush et al., 1991; Sirotnik, 1980).

The analysis of intervention effects on youth outcomes must incorporate the nesting of individuals within communities and the random assignment to conditions at the community level. Thus, the analyses need to incorporate multilevel models that take this nesting into account and provide unbiased estimates of standard errors (Bryk et al., 1996; Hox, 1998; Murray, 1998). The CTC intervention is expected to produce community-level changes in prevention service system characteristics, for example, increased collaboration among service providers and increased use of science-based prevention strategies. These changes in service systems characteristics are expected to produce student-level changes in risk and protective factors. These changes in risk and protective factors are expected, in turn, to affect changes in self reported adolescent drug use and related problem behaviors. The sections below describe both cross sectional and longitudinal comparisons of intervention and control communities.

**Aim 1.** To test the effectiveness of the CTC system in reducing risk, increasing protection and reducing problem behaviors.

Cross-sectional cohort analyses. Analyses for Aim 1 will begin by testing differences between the intervention and control communities for each grade each year on both specific and composite measures of risk and protective factors derived from the cross-sectional student surveys. These analyses will compare levels of specific risk and protective factors targeted by multiple intervention communities and composite measures of total risk and protection within each of four domains: community, school, family, and peer/individual. Multilevel General Linear Modeling techniques (Bryk & Raudenbush, 1992; Heck & Thomas, 2000; Murray, 1998), in which children are nested within communities, and communities nested within the matched pair, will be used. Analyses using the matched pairs design are proposed here because power analyses demonstrated that for most outcomes the matching, which assures that the intervention and control groups are similar on key variables at baseline, reduces the error variance in the dependent variables. Treatment will be modeled as a fixed effect predicting differences between communities within pairs. Alternately, school-level effects will be assessed through analyses nesting children within schools and schools within communities, using unmatched designs. Community-level covariates will be added to these models to reduce the community-level variance and, thus, increase the power of the analyses. For example, a community-level archival indicator of poverty such as those collected for the Diffusion project (e.g., unemployment, free and reduced lunch enrollments, etc.) will be entered as a time-varying covariate in some models to control for possible economic differences between communities. Community-level covariates will be limited to maintain the degrees of freedom available for testing the effects of intervention. Child-level covariates, such as gender, will be added to understand more about how the intervention affects different adolescents.

The analysis will then assess the effects of intervention on changes over time in communities' levels of risk and protective factors. These analyses will use growth curve models (Bryk & Raudenbush, 1987; Diggle et al., 1995) at the community level to examine the effect of intervention on slopes of risk and protection over time. These are flexible models that allow the use of individual covariates and community-level time-varying covariates. Standard multilevel models will be used, with four levels of nesting: children at level one nested within survey occasion at level two, nested within communities at level 3, and nested within pairs at level 4. In this model, growth curves exist at level 2, in which the community average scores at each time point are modeled as a function of an intercept and slope that represents change over time. Again, treatment is a fixed community-level effect that predicts the slope of the growth curve at level 3.

In the analyses above, intervention condition is used as a predictor of differences and changes in risk and protective factors. We will also assess the effect of the intervention by examining the relationship between community implementation of the CTC strategy and risk, protection, and adolescent behavior outcomes. As described earlier, the CKI interviews conducted in the second and fourth year of the study will provide data to create implementation scores for each community. These are ratings of the extent to which each community has advanced in implementing the CTC strategy on a scale of 1 to 5. Using implementation scores in analyses will allow assessment of whether variation in the degree to which the CTC intervention was implemented is related to differential outcomes. These analyses follow those above and will use the implementation score as an independent variable at the community level.

One of the major strengths of this study is that multiple years of baseline data are available for each of the communities. This allows us to posit growth models that go beyond describing differences in slopes by taking into account community-level slopes from before the intervention. Thus, the ability of the intervention to produce positive or negative trends within each community can be assessed. Community trends can be taken into account using Bayesian estimates of the baseline slopes and intercepts within each community as covariates when predicting differences in the slope and intercept due to intervention (e.g., Bryk & Raudenbush, 1992). Use of the multiple baseline data points allows us to assess stability, or variance over time, of measures within each community.

These analyses will be extended to address Aim 4 to test the degree to which the use of tested programs in communities affects children's risk and protection exposure and behavior outcomes. The intervention is expected to increase collaboration and the use of effective interventions targeted at priority risk and protective factors. These variables can be used as community-level predictors to test whether they mediate the effect of the intervention on outcomes using the growth modeling approach.

Analyses of the effects of intervention on adolescent drug use and related behavior will be conducted using logit models that assess the effects of the intervention on the likelihood that children within each community engage in each of the targeted behaviors, initiation of alcohol, cigarette, and marijuana use, and incidence of delinquent and violent behavior. For example, we can begin analyses looking at the effects of intervention on reported alcohol use, a child level dependent variable at a single time point. A three level model in which children's reported alcohol use is treated as nested within community, and community is nested within the matched pair, will be used. The intervention will be considered a fixed effect at level 2. Again, in some models, school, instead of the matched pair, will be entered as a level. Analyses also will seek to assess intervention effects on growth in alcohol use across grades by combining grade level samples and entering grade as a covariate at the child level 1. This model can then be used for a longitudinal assessment of the effects of intervention on changes over time in the prevalence of alcohol use at the community level. Using HLM (Bryk & Raudenbush, 1992; Bryk et al., 1996) terminology and a logit link to model the binary outcome the model would be written:

|                           |                                                                                                                                                                                            |
|---------------------------|--------------------------------------------------------------------------------------------------------------------------------------------------------------------------------------------|
| Level-1, students         | Probability of alcohol use ( $Y = 1$ ) = $\phi_{ijkp}$
$\log(\phi_{ijkp}/1 - \phi_{ijkp}) = \pi_{0jkp} + \pi_{1jkp} \text{Grade}$                                                       |
| Level-2, survey occasions | $\pi_{0jkp} = \beta_{00kp} + \beta_{01kp} \text{Year} + r_{0jkp}$
$\pi_{1jkp} = \beta_{10kp}$                                                                                           |
| Level-3, communities      | $\beta_{00kp} = \gamma_{000p} + u_{00kp}$
$\beta_{01kp} = \gamma_{010p} + \gamma_{011p} \text{Treatment} + u_{01kp}$
$\beta_{10kp} = \gamma_{100p} + \gamma_{101p} \text{Treatment}$ |
| Level-4, pairs            | $\gamma_{000p} = \zeta_{0000} + w_{000p}$
$\gamma_{010p} = \zeta_{0100} + w_{010p}$
$\gamma_{011p} = \zeta_{0110} + w_{011p}$                                                        |

$$\gamma_{101p} = \zeta_{1010} + w_{101p}$$

This model postulates that the probability of an individual reporting alcohol use is a function of their grade and the average alcohol use at time  $j$  in community  $k$  within pair  $p$ . The growth portion of the model occurs at level 2, in which the proportion of youth within each community at a given time point using alcohol is modeled as a function of the initial alcohol use in that community and the slope related to the year of observation. At the community level, the effect of the intervention on change within communities and the relationship of grade to alcohol use is tested. Note that this is actually testing the interaction of the linear growth component with treatment and of the relationship of grade to outcomes with treatment. This is true because the model postulates that the slope of the growth curve varies as a function of treatment, the definition of an interaction. These four level models will be modeled in MLwiN (Rasbash et al., 2000), which allows for more than three levels of nesting.

Given that not all of the risk and protective factors are expected to be normally distributed, the assumption of normal and independently distributed errors within each level of nesting may not be appropriate (Feng et al., 2001). Permutation tests which do not make this assumption are available in group-randomized designs. The appropriateness of using these models will be examined. It is also possible to pose models other than growth models in testing the relationship of the intervention to change in outcomes. While we believe that growth models are reasonable, given that exposure will increase and services are expected to improve over the course of the study, thus improving outcomes, the fit of these models will be examined and other options considered if necessary.

Analyses of the longitudinal panel. Use of a longitudinal panel allows examination of how the intervention affects children as individuals rather than groups over time. We expect the potentially wide variation in individual-level growth curves will be hidden in group-level analyses. The individual-level longitudinal analyses will be powerful because they can account for differences between individuals in rates of change. These longitudinal analyses will involve the use of multilevel models and growth curve modeling as described above for risks and protection, but with the longitudinal sample the growth curves will be specified at the child level rather than the community level. The effects of treatment condition on average slopes within communities will be modeled at the community level. In order for these models to work, risk and protective factors must follow a growth pattern that can be identified and modeled. Previous work has shown that it is possible to specify individual level growth curves for risk and protective factors and that differences in their slopes can be predicted by involvement in intervention (Hawkins et al., in press). Effects of the intervention on substance use and problem behavior will be examined using three level logistic models in which engaging in substance use or problem behaviors by the eighth grade is modeled as a function of the intervention.

The longitudinal panel data also will allow examination of subgroups of children most affected by the intervention. For example, students experiencing moderate to high levels of risk exposure are more likely to be affected by intervention than students experiencing low levels of risk. We will assess whether initial levels of risk and protection are differentially related to changes in risk and protection in the intervention and control groups. This can be tested using a model in which baseline risk is a covariate predicting slopes of risk at the individual level, and then assessing the effect of the intervention on this relationship at the community level. Interactions between a variety of individual level effects and the intervention can be examined in this manner to better understand for whom the intervention has the largest effects. We have an ongoing consulting relationship with [name] who will serve as an advisory board member for the proposed project and will assist in the specification of multilevel analysis models.

**Aim 2.** To examine effects of CTC on levels of collaboration across agencies, groups and organizations in communities.

**Aim 3.** To examine effects of CTC on community use of epidemiologic data to guide prevention service system planning.

Aims two and three address the effects of the CTC intervention on community-level outcomes. Community outcome analyses will be conducted using single level models since the outcomes are viewed as characteristics of the community. Since the analyses for both aims are the same, they are described together. Both cross sectional and longitudinal analyses will be conducted to assess average differences and changes in collaboration or use of epidemiological data over time as they relate to the intervention.

Differences between treatment and control communities in community-level outcomes will be assessed using standard General Linear Models (GLMs). Community covariates will be used to reduce the error

variance of each model and help explain reasons for differences between communities. Further longitudinal analyses using growth curves will assess the effects of intervention on changes in collaboration and use of epidemiologic data for strategic prevention planning over time. These growth curves can be assessed using either multilevel GLM techniques or structural equation models. The advantage of using structural models is that they allow more efficient modeling of ordinal variables providing more accurate estimates of parameters and standard errors (Muthén et al., 1997). These analyses will also utilize the information available for these communities for the five years prior to intervention. One method, as described above, for looking at student outcomes, is to use the slopes and intercepts from the baseline period as predictors of the slopes during the intervention period. This allows for assessing whether the intervention is able to change trajectories across time.

As in the first aim, comparisons of treatment and control communities will be elaborated by separate analyses testing the extent to which CTC implementation relates to these community-level outcomes.

**Aim 4.** To assess the degree to which the use of tested effective programs in communities predicts changes in community-wide levels and trajectories of risk, protection, and drug use and related health and behavior outcomes.

Analyses for this aim are similar to those in Aim 1; the outcomes are measures of risk and protection and substance use and delinquent behavior at the student level and both cross-sectional models examining the relationships year by year and longitudinal models at the community level will be tested. Three- and four level HLM analyses will be used to assess these relationships as discussed above. We will begin by examining the overall relationship between total number, scope, dosage, and exposure of tested programs across all categories, as described above in the measures section, to composite measures of risk, protection, and outcomes. We will then elaborate these tests by examining the number, scope, dosage, and exposure of specific types of prevention programs (e.g., parenting skills training) and their relationship to changes in specific risk and protective factors (e.g., family management problems, parent-child bonding, etc.). We will also elaborate these tests by examining these relationships at the school building, rather than community level. The use of continuous and ordinal level predictors does not affect the specification of the multilevel models described above.

Given a relationship between these community-level outcomes and student outcomes and an effect of the intervention on student outcomes in Aim 1, these analyses will be further elaborated to examine the CTC framework. Specifically the framework posits that the intervention will positively affect youths through its impact on community prevention service system characteristics such as use of science-based strategies. We propose to examine this aspect of the framework by expanding on the results of the above analyses and testing a mediation model that examines the extent to which the community-level outcomes account for all or most of the effect of treatment on students. This can be examined by entering the community outcomes into the final models from Aim 1 as predictors at the community level. If the intervention is affecting students solely through programmatic effects at the community level, the treatment effect should become zero in this model. This mediation model can then be expanded with a longitudinal model in which community-level outcomes predict changes in student outcomes over the course of the study. These relationships will be examined in both the cross sectional data and in the longitudinal panel. Although theoretically more complex, these analyses are relatively simple expansions of the models used to assess Aim 1.

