### **Sample**

**Community selection.** Thirteen pairs of communities participating in the Diffusion study were eligible for inclusion in this study, and 12 pairs have been recruited for the proposed study. These communities have demonstrated their commitment to participate in SDRG research by providing a variety of data for the Diffusion project. In all these pairs, neither community has progressed to the point of installing tested effective policies and programs to address prioritized community risk and protective factors. We have randomly assigned these matched communities to the intervention or control condition. The CTC intervention is expected to produce measurable changes in the prevention service systems in the communities which, in turn, are expected to affect levels of risk, protection, and outcomes among youth aged 9 to 14 over the study period.

The 24 communities in the study were matched with regard to size, poverty and crime indices for the Diffusion project. For the proposed study, this matching maximizes the baseline comparability between the experimental and control communities and reduces potential threats to study's internal validity. Analysis of student survey data from the 1998 and 2000 survey administrations in these communities revealed no significant differences between the intervention and control communities with regard to levels of risk and protective factors or drug use outcomes. Table 2 provides descriptive data on the characteristics of the intervention and control communities

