### **Power**

The proposed study builds on a descriptive study that provides baseline data for all proposed sites. This allows us to use parameter estimates from the sample under study to estimate the power of the proposed study to detect effects. Analyses have been conducted using data from each study community collected in 2000. Thus, our power analyses provide very accurate assessments of the differences between intervention and control groups that can be observed with adequate power.

The power analyses for adolescent outcomes assume that children are nested within communities. A three level structure in which students are nested within schools nested within communities is also possible. Separate three level power analyses were conducted and only small differences were found for the more complex design. Further, all analyses assumed continuously varying, normally distributed outcomes. While this assumption is violated for binary outcomes, simulations have found that, given at least 30 members per group, the Central Limit Theorem still holds and the analyses will still provide adequate parameter estimates (Hannan & Murray, 1996).

Power was estimated for analyses using a simple comparison of the experimental and control groups, then for analyses using a matched pair design, and finally for analyses using matched pairs in which

1998 average community levels of each outcome is included as a community-level baseline covariate. While the longitudinal data we have for the communities does not yet extend for more than two years, including the 1998 scores allows an assessment of the ability to detect how the intervention is related to change in communities rather than just differences in community means. The principal task in power analyses is to find an estimate of the variance of the treatment effect,  $\sigma\Delta$ . Then t-statistics can be calculated and formulas can be applied to find the power for any given treatment effect. As described in Appendix G, the power of the proposed study was calculated by first finding the standard error of the treatment effects (Bryk & Raudenbush, 1992; Murray, 1998; Raudenbush, 1997; Raudenbush et al., 2000) and then using these standard errors to find the detectable treatment effect with a power of .80.

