Estimates of  $\sigma\Delta$  were found by using data from the study communities. Since the community is the level of random assignment, the sample size is 24 (Murray, 1998). Analyses were done using only eighth grade students since that is the grade expected to be most directly affected by the intervention. For the sake of brevity, two representative risk factors and the most relevant behavioral outcomes for the targeted age group were used in the power analyses.

We found that in most cases use of the matched pairs design reduced the community-level variance enough to result in an increase in power even when taking into account the loss of degrees of freedom. Further, the addition of 1998 baseline outcome measures as community-level covariates generally resulted in large decreases in community-level variance resulting in further increases in power. The power of the matched pairs analyses with community-level covariates is reported in Table 3. For a full description of these analyses, see Appendix G.

Results of these analyses indicate that this study has adequate power to detect differences in student's risk and protective factors equivalent to a small effect size of .25. Effect sizes of .2 or larger are generally considered to be small but of practical significance, while effect sizes of .50 and above are generally considered large in social science research (Cohen, 1977). The study has power to detect differences of 12% in rates of lifetime use of alcohol, 7% in rates of lifetime use of cigarettes, and 7% in rates of alcohol use during the past month (a 22, 16, and 25% reduction, respectively). Average prevalence rates for these variables are reported in Table 3 in the means column. These effects are at the low end of the range of what has been demonstrated by other successful community-level interventions which have found reductions in initiation of alcohol and cigarette use in the eighth grade of between 20 and 40% (Pentz et al., 1997; Perry et al., 2000; Perry et al., 1996). The detectable difference for risk factors is based on the 4-point scale measuring these constructs.

The power reported here for the child level outcomes is expected to be the minimum that is observed in the longitudinal analyses both at the community level and at the child level in the longitudinal panel.

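### Table 3's power assumes adjustment for each outcome's 1998 community level, but the single-time-point and panel behaviour models do not name that covariate

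*Protocol*

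**What the plan says.** Power section: three designs were examined, the last being matched pairs in which "1998 average community levels of each outcome is included as a community-level baseline covariate". The text then says "The power of the matched pairs analyses with community-level covariates is reported in Table 3", and reports that "the addition of 1998 baseline outcome measures as community-level covariates generally resulted in large decreases in community-level variance". It expects this power to be the minimum for the longitudinal analyses, both at community level and in the child panel.

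Analysis, Aim 1, describes the models:
- **Risk and protection, each grade and year:** community-level covariates are promised in order to reduce variance and raise power. The only community-level example is a poverty indicator, used in some models, and the number of such covariates is to be limited.
- **Single-time-point behaviour model:** "A three level model in which children's reported alcohol use is treated as nested within community, and community is nested within the matched pair", with the intervention fixed at level 2. No baseline outcome is named.
- **Panel behaviour:** a three-level logistic model in which "engaging in substance use or problem behaviors by the eighth grade is modeled as a function of the intervention".
- **Growth models:** pre-intervention slopes and intercepts are offered as possible covariates. The written four-level model places Treatment on the Year and Grade slopes, not on the community intercept.

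On comparability, the Sample section says that the 1998 and 2000 surveys "revealed no significant differences between the intervention and control communities with regard to levels of risk and protective factors or drug use outcomes". Table 2 gives eighth-grade prevalences by arm.

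**The concern.** The power calculation and the analysis describe different models. The covariate that the Power section credits with a large variance reduction is not the one named in the level models (those comparing arms at one time point) or in the panel behaviour model. With 12 pairs there is room for very few community-level covariates, so it matters which one is fixed in advance.

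Two things are at stake. The first is precision: a model without the baseline outcome has a larger standard error than Table 3 assumes. The second is the estimate in this particular allocation: every behaviour in Table 2 is lower in the intervention arm. Absence of significance is weak reassurance, because a gap half the size of the detectable effect would not be expected to reach significance with 12 pairs.

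**Working it through.** **Inputs from the protocol.** 12 pairs ("12 pairs have been recruited for the proposed study"). Average grade enrolment 316 at 70% usable, so 316 × 0.70 ≈ 221 students per grade per community. Table 3 means and detectable differences: lifetime cigarettes 0.43 and 0.078; lifetime alcohol 0.52 and 0.130; 30-day alcohol 0.27 and 0.078; delinquency 0.22 and 0.075. Power .80 ("using these standard errors to find the detectable treatment effect with a power of .80").

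**Assumptions.** Two-sided alpha .05 (not stated); 10 degrees of freedom with one covariate and 11 without; equal community sizes; correlation r between a community's baseline and outcome level after pairing, taken as .3, .5 and .7 (not given; the details are in Appendix G, which is not in the document).

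**Table 3's own figures.** The differences cannot be rebuilt without Appendix G. The percentage column can be checked: .078/.43 = 18.1% (printed 18), .130/.52 = 25.0% (25), .078/.27 = 28.9% (29), .075/.22 = 34.1% (35). The Power text gives somewhat different figures for three of these outcomes; Table 3 is used here.

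**Step 1, implied adjusted SE.** Detectable difference = SE × (t.975 + t.80). At 10 df the multiplier is 2.228 + 0.879 = 3.107. Cigarettes: .078/3.107 = .0251. Alcohol: .130/3.107 = .0418.

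**Step 2, remove student sampling variance,** which a community covariate does not reduce: 2p(1−p)/(221 × 12). Cigarettes: .4902/2652 = .000185, leaving a community part of .000630 − .000185 = .000445. Alcohol: .4992/2652 = .000188, leaving .001750 − .000188 = .001562.

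**Step 3, take the covariate out.** Unadjusted SE = √[community part/(1−r²) + student part]. Cigarettes at r = .5: √(.000445/.75 + .000185) = .0279. Power comes from the noncentral t at 11 df with noncentrality .078/.0279 = 2.80, which gives 72%.

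| Outcome | Power at Table 3's difference, r = .3 / .5 / .7 | Detectable difference at 80% power |
|---|---|---|
| Lifetime cigarettes (.078) | 78% / 72% / 59% | .080 / .086 / .100 |
| Lifetime alcohol (.130) | 77% / 70% / 55% | .134 / .147 / .175 |
| 30-day alcohol (.078) | 78% / 71% / 58% | .080 / .087 / .102 |
| Delinquency (.075) | 78% / 71% / 57% | .077 / .083 / .098 |

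Inflating the whole SE, student error included, would give 77% / 69% / 53%. That overstates the loss.

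**Step 4, Table 2 imbalance (intervention minus control).**

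| Behaviour | Gap | Share of Table 3's detectable difference |
|---|---|---|
| Lifetime cigarettes | .41 − .45 = −.04 | .04/.078 = 51% |
| Delinquency | .21 − .23 = −.02 | .02/.075 = 27% |
| 30-day alcohol | .27 − .28 = −.01 | .01/.078 = 13% |
| Lifetime alcohol | .51 − .52 = −.01 | .01/.130 = 8% |
| Lifetime marijuana | .18 − .22 = −.04 | not in Table 3 |
| 30-day cigarettes | .14 − .17 = −.03 | not in Table 3 |

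If community spread is similar at both times, the expected carry-over is r × gap. For lifetime cigarettes that is 1.2, 2.0 or 2.8 points at r = .3, .5 or .7. For either alcohol measure it is under 1 point.

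**The case against.** A reader might infer that the plan excludes the baseline outcome. For risk and protection it does not: community covariates are promised for the same variance-reducing purpose, and poverty is only an example. There the covariate is not named rather than ruled out, and a separate analysis plan could name it. The single-time-point logit is also introduced as an illustrative first step. What stands is that the document rests its power on one specific covariate and then describes the behaviour models without it.

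A reader might also infer that the Aim 1 results would be biased. Assignment was by coin toss within matched pairs, so the unadjusted contrast is unbiased over randomisations and its test is valid. The six behaviours are related measures on the same students, not six independent signals, and the two alcohol gaps are 1 point each. Only a lean conditional on this imbalance can be claimed. Nor does the concern reach the written four-level model of change over years, where Treatment acts on slopes.

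For the panel, Table 2 describes eighth graders surveyed before the study, not the fourth-grade cohort's own baseline, so it shows community-level imbalance only. It is tempting to say that the panel model counts children who had already used at Wave 1 as failures. The text does not say whether they are in the denominator, and elsewhere it frames the panel around initiation. The denominator is unspecified, which is a smaller matter.

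Finally, r is unknown. The large variance reduction was seen over 1998 to 2000, while outcome surveys run to 2007 in different cohorts, so r may be at the low end, where the loss is 2 to 3 percentage points.

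**Conclusion.** The mismatch is real and worth correcting. Table 3 applies to the baseline-adjusted matched-pair analysis. The single-time-point behaviour model and the panel behaviour model, as described, are not that analysis, and the risk and protection models do not commit to it. Run without the covariate, power at Table 3's differences falls from 80% to somewhere between 78% and 55% for lifetime cigarettes and lifetime alcohol. The position in that range depends on a correlation the document does not give. The lean in the estimate is about 1 to 3 points for lifetime cigarettes and negligible for alcohol. No panel-specific loss can be computed, because no fourth-grade rates are given.

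**What to change.** In the Aim 1 risk and protection level models and the single-time-point behaviour model, name the pre-intervention community level of the same outcome as a fixed community-level covariate, ahead of poverty indicators. Use at least the 1998 level assumed in the power calculation; the mean of the available Diffusion baseline waves is an alternative. In the panel behaviour model, adjust for the child's Wave 1 value and, for initiation outcomes, restrict the analysis to children who had not used at Wave 1. If the covariate is not wanted, restate Table 3 without it.

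The cost is a wording change and one community-level degree of freedom, which a power calculation for the adjusted design should already have spent. The community baseline data are in hand. Wave 1 panel data are already planned but not yet collected, so no extra data collection is needed.
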